### Recruitment {15}

Recruitment is planned over a period of 24 months. The rate of one patient per center per 2 months makes this recruitment target completely achievable.

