**Methods:**

Our hypothesis is that phycocyanin may give protection against oxaliplatin-induced neuropathy in the treatment of gastrointestinal cancers. Our trial will be a randomized double-blind placebo-controlled study with 110 randomized patients suffering from metastatic gastrointestinal adenocarcinoma including esogastric, colorectal, and pancreatic cancers. Patients are being followed up in the gastroenterology or oncology departments of seven French hospitals.

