## Methods: participants, interventions, and outcomes

### Study setting {9}

This study is a French multicenter trial. Patients will be recruited from seven teaching hospital gastroenterology departments: CHU Nantes, Foch Hospital, Vendée Departmental Hospital, Estaing Hospital, Saint-Grégoire Private Hospital, Saint Nazaire Hospital, Georges and François Leclerc Center.

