### Sample size {14}

Simon’s two-stage design [15] will be used. The null hypothesis that the true response rate is 0.60, the proportion of neurotoxicity targeted, will be tested against a one-sided alternative. In the first stage, 31 patients will be accrued. If there are 18 patients or fewer with grade 1 neurotoxicity among these 31 patients in the SLPC arm, the study will be halted. Otherwise, 24 additional patients will be accrued, making a total of 55. The null hypothesis will be rejected if 38 or more responses are observed in 55 of the SLPC arm patients. With a type I error rate of 0.05 and a power of 0.90, 55 patients will be enrolled in each arm, that is to say, 110 patients.

All the previous hypotheses account for a lost-to-follow-up rate at 4 months of 20%.

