## Trial status

This trial has just started.

The updated protocol is at version 2 as of May 23, 2022.

The first patient was enrolled in April 2022.

Recruitment by the investigating centers is planned to continue until April 2024.

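### At the stated rate, seven centres recruit 84 patients in 24 months, not the 110 the protocol calls achievable

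*Protocol article*

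**What the plan says.** All the figures needed are in the protocol article.

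- **Period.** Recruitment {15}: "Recruitment is planned over a period of 24 months". Trial status gives the first enrolment as April 2022 and adds: "Recruitment by the investigating centers is planned to continue until April 2024". The two sections agree on about 24 months.
- **Rate.** Recruitment {15}: "The rate of one patient per center per 2 months makes this recruitment target completely achievable".
- **Centres.** Study setting {9}: "Patients will be recruited from seven teaching hospital gastroenterology departments", followed by a list of seven. The Methods paragraph of the abstract agrees: "Patients are being followed up in the gastroenterology or oncology departments of seven French hospitals".
- **Target.** Sample size {14}: "55 patients will be enrolled in each arm, that is to say, 110 patients". The abstract describes a "randomized double-blind placebo-controlled study with 110 randomized patients".
- **Losses.** Sample size {14} states that the design assumptions already allow for 20% loss to follow-up at four months.

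**The concern.** The recruitment rate is given as the reason the target can be met. It is therefore a feasibility claim that can be checked against the article's own number of centres, period and target, and it fails that check.

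The consequence is practical. The timetable in Recruitment {15} and Trial status cannot be met at the rate on which it is based. Either accrual runs past April 2024, or the trial closes short. In the second case the Simon rule in Sample size {14}, which rejects on 38 or more responses among 55 SLPC patients, has no direct application to an arm of about 42.

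**Working it through.** **Inputs**

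| Input | Value | Source |
|---|---|---|
| Centres | 7 | Study setting {9}; abstract, Methods |
| Period | 24 months | Recruitment {15}; Trial status |
| Rate | 1 patient per centre per 2 months = 0.5 per centre per month | Recruitment {15} |
| Target | 110 randomized, 55 per arm | Sample size {14}; abstract, Methods |

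**Step 1: try to reproduce 110.**
Expected accrual = centres × months × monthly rate = 7 × 24 × 0.5 = **84**, which is 84 / 2 = 42 per arm under 1:1 allocation.
Shortfall = 110 − 84 = **26**, and 26 / 110 = 24%.

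This is a favourable figure, since it assumes that all seven centres recruit throughout. Staggered opening would lower it.

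**Step 2: try other readings of the inputs.**
- April 2022 to April 2024 counted inclusively as 25 months: 7 × 25 × 0.5 = 87.5.
- Eight centres: 8 × 24 × 0.5 = 96, or 8 × 25 × 0.5 = 100 over 25 months.
- Nine centres: 9 × 24 × 0.5 = 108, close to the target, but the article gives seven in two places.

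No reading with seven or eight centres reaches 110.

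**Step 3: does the loss allowance explain the gap?**
No. Sample size {14} says: "All the previous hypotheses account for a lost-to-follow-up rate at 4 months of 20"%. The allowance is thus described as already included, and the abstract counts 110 as randomized. Recruitment has to deliver 110, and losses come afterwards.

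**Step 4: what would reach 110, changing one input at a time?**
- Period: 110 / (7 × 0.5) = 31.4 months, so about 32.
- Rate: 110 / (7 × 24) = 0.655 per centre per month. Two per centre every three months is 0.667, and 0.667 × 168 centre-months = 112.
- Centres: 110 / (24 × 0.5) = 9.2. Nine give 108 and ten give 120, so ten in whole centres.

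**The case against.** **The rate may be a cautious minimum.** A sponsor may quote a low rate and expect to exceed it. The wording does not say so: the rate is offered as what makes the target achievable, and at that rate it is not. Chance variation does not rescue it either. If accrual were Poisson with mean 84 (an assumption), the probability of reaching 110 would be about 0.4%.

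**The dates are only plans.** This stands. Both sections say that recruitment is planned to that point, and nothing commits the trial to closing in April 2024 whatever the count. An extension of 31.4 − 24 = 7.4 months at the same rate would leave the design and the analysis intact.

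**A reader might infer that the trial is left with almost no power.** Keeping the threshold of 38 with only 42 SLPC patients would demand 38 / 42 = 90% observed responders. The documents do not support that inference. The threshold is tied to 55 patients, and nothing says it would be kept for a smaller arm. Nor does Sample size {14} state an alternative response rate. A value of 0.80 can only be inferred, by halving the 40% toxicity implied by a null response of 0.60. As an illustration, keep the first-stage rule (stop at 18 or fewer of 31) and reject at 31 or more of 42. The type I error is then 0.045, and the power is 0.88 at an assumed true response of 0.80 (0.65 at 0.75 and 0.98 at 0.85), before losses. Closing short would cost some power, but it does not imply a collapse.

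**A reader might also want a rule for recomputing the boundaries, or object that the interim look comes late in accrual.** Neither belongs to this point. A rule for under-recruitment may stand in the full protocol or analysis plan, which are not shown. The overlap of the interim look with accrual follows from the open statement under Interim analyses {21b} that enrolment continues during the futility analysis.

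**Conclusion.** The contradiction is exact and rests only on the article's own figures: 84 expected patients against 110, a shortfall of 26 (24%). The assumptions are that the rate applies to each of the seven centres and that all of them recruit for the full 24 months; the second favours the plan. The feasibility statement is wrong as written.

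The severity is minor. The rate enters no boundary, error rate or estimate, so the error does not by itself alter the Simon design or the analysis. The one design consequence is conditional: if recruitment did close at about 42 SLPC patients, the final rule for 55 could not be applied as it stands.

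**What to change.** Restate Recruitment {15} and Trial status so that rate, period and number of centres agree with 110, and bring Study setting {9} into line if centres are added. Any one of these suffices:

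- keep seven centres and the stated rate, and plan about 32 months;
- keep seven centres and 24 months, and state a required rate of about 0.66 per centre per month, for example two per centre every three months;
- keep the stated rate and 24 months, and plan about ten centres.

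The cost is a corrected sentence or two, plus an amendment if the recruitment period is extended or centres are added. The sample size, the Simon boundaries and the analysis need no change on this account.

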## Assignment of interventions: allocation

### Sequence generation {16a}

Randomization will be conducted blindly by center, neuropathy (stage 0 or 1), and age (< 65 years old and ≥ 65 years old). Wrongly enrolled randomized patients will not be replaced. It will be block balanced in a 1:1 ratio. The software used for the randomization is SAS version 9.4.

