### Objectives {7}

The primary objective is to demonstrate a 50% decrease in neurotoxicity grades of 2 or above at cycle 9 (4 months after the start of oxaliplatin-based chemotherapy) in the SLPC arm.

The secondary objectives are to compare the following in both arms:➢ Percentage of patients who stopped oxaliplatin due to neurological toxicity➢ Percentage of patients with an oxaliplatin dose decrease➢ Neurological toxicities according to the Common Terminology Criteria for Adverse Events (CTCAE) v5.0➢ Overall toxicity (including hematological toxicity, gastrointestinal toxicity, etc.)➢ Patient’s quality of life according to the EORTC-QLQ-C30 questionnaire

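### The final cut-off of 38 of 55 gives a one-sided type I error of 0.104, not 0.05, and stratified blocks and 20% loss mean that 55 is not guaranteed

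*Protocol article*

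**What the plan says.** Sample size {14} of the protocol article sets up a Simon two-stage design in the SLPC arm. It gives "The null hypothesis that the true response rate is 0.60", which "will be tested against a one-sided alternative". On stage 1, "In the first stage, 31 patients will be accrued", and the study stops if 18 or fewer respond. With 24 more patients, the final rule is that "The null hypothesis will be rejected if 38 or more responses are observed in 55 of the SLPC arm patients". The claimed properties are: "With a type I error rate of 0.05 and a power of 0.90, 55 patients will be enrolled in each arm". The section adds that its assumptions allow for 20% loss to follow-up at 4 months.

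Trial design {8} calls the trial non-comparative and not powered to compare the arms, so this count is the only decision rule stated.

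On allocation, Sequence generation {16a} says: "Randomization will be conducted blindly by center, neuropathy (stage 0 or 1), and age" (under 65, or 65 and over), in 1:1 blocks. Study setting {9} lists seven centers. The article gives no block size. The section on non-adherence and missing data {20c} bases estimates on a modified intention-to-treat population.

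**The concern.** Two things need to hold for the final rule to do its job. The cut-off must have the stated error rate at the planned size, and the size analysed must be the one for which the cut-off was set.

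The first can be checked exactly, and it fails. The second is doubtful for two reasons. Small strata leave unfinished blocks, so the SLPC arm is a random number near 55. Loss to follow-up then lowers the number with a 4-month outcome. A threshold on a raw count is sensitive to its denominator: a few patients more or fewer change the chance of a false positive several-fold. At stake is whether a positive result carries the 5% false-positive risk that readers will be told it has.

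**Working it through.** **Inputs from the article.** Null rate 0.60; stage 1 of 31 patients, stopping at 18 or fewer; 24 more to reach 55; rejection at 38 or more; one-sided type I error 0.05; power 0.90; 20% loss.

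**Assumptions.** The article states no alternative response rate. I take 0.80: if 40% have grade 2 or above under the null, halving that, in line with the objective to "demonstrate a 50% decrease in neurotoxicity grades of 2 or above at cycle 9", leaves 20%. The type I error results do not depend on this. Stage 1 is taken to contain exactly 31 patients with an outcome.

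**Formula.** For a final number n and cut-off r,

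P(reject) = sum over x = 19 to 31 of Bin(x; 31, p) × P[Bin(n − 31, p) ≥ r − x].

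**Step 1: the plan's own rule (n = 55, r = 38).**
- Type I error at p = 0.60: 0.1042 (stated: 0.05).
- Power at p = 0.80: 0.980 (stated: 0.90).
- Reading the interim rule as fewer than 18, as Interim analyses {21b} has it, gives 0.1061. Ignoring stage 1 gives 0.1066. Neither explains the gap.
- With r = 39, type I error is 0.062. With r = 40 it is 0.0345, with power 0.931. So 40 is the smallest cut-off at 55 that holds 0.05.

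**Step 2: how firm is 55?** Fully crossed strata: 7 × 2 × 2 = 28, and 110 / 28 = 3.9 patients each on average. Permuted blocks were simulated within strata, with 110 randomised, 20,000 allocations per setting, equal or unequal centers, half of patients in each age group, and neuropathy stages split 90/10 or 50/50.

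| Assumed block size | Exactly 55 in SLPC arm | Central 95% range |
|---|---|---|
| 2 | 21–23% | 51–59 or 52–58 |
| 4 | 16–18% | 50–60 or 51–59 |
| 6 | 13–16% | 49–61 or 50–60 |

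**Step 3: loss to follow-up.** The article says "55 patients will be enrolled in each arm, that is to say, 110 patients", so 55 is an enrolled number. After 20% loss, 0.80 × 55 = 44 remain. Having 55 with an outcome would need 55 / 0.80 = 68.75, that is 69 per arm.

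**Step 4: 38 kept at other sizes, against a recalibrated cut-off.** The recalibrated cut-off is the smallest r with exact type I error at or below 0.05, given 18/31 at stage 1.

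| n | Type I error, r = 38 | Power at 0.80, r = 38 | Recalibrated r | Type I error | Power at 0.80 |
|---|---|---|---|---|---|
| 44 | 0.0001 | 0.196 | 33 | 0.028 | 0.846 |
| 50 | 0.013 | 0.814 | 37 | 0.028 | 0.889 |
| 52 | 0.035 | 0.918 | 38 | 0.035 | 0.918 |
| 53 | 0.053 | 0.948 | 39 | 0.028 | 0.906 |
| 55 | 0.104 | 0.980 | 40 | 0.035 | 0.931 |
| 58 | 0.216 | 0.994 | 42 | 0.034 | 0.941 |
| 60 | 0.298 | 0.995 | 43 | 0.041 | 0.956 |

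**Step 5: average effect of chance arm size.** Weighting the r = 38 type I error by the simulated arm sizes (blocks of 2 to 8) gives 0.112 to 0.129, against 0.104 at exactly 55. Blocking therefore adds about 1 to 2.5 percentage points.

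**The case against.** The strongest reply is that the article ties 38 to a denominator of 55 and never says that 38 would be kept at 50 or 60. Recalibrating a Simon cut-off to the number reached is commonly left to the statistical analysis plan, which is not shown. Small imbalance is ordinary in any stratified blocked trial, and most simulated allocations land within three patients of 55. On average the imbalance costs little (step 5). A modestly smaller arm can even help: at 52, a cut-off of 38 meets both stated properties.

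All of this stands, and it limits the point. A reader might infer that this randomisation cannot yield 55 SLPC patients, that the plan applies 38 at any size, or that chance arm size is what spoils the test. The documents support none of these. The scheme can yield 55 but does not guarantee it. The spread from 0.013 to 0.298 is conditional on the size reached and on keeping 38. Nor would reaching exactly 55 cure the test, since the error rate is already 0.104 there.

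What the reply does not touch is that last result. It uses only figures printed in Sample size {14} and needs no assumption about blocks, loss or the alternative.

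**Conclusion.** The point holds as an error in the stated cut-off, aggravated by uncertainty about the denominator. At 55 patients the rule has about twice the stated type I error (0.104 against 0.05). Power at an assumed response rate of 0.80 is 0.980 rather than 0.90.

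Chance arm size is secondary. Expected loss matters more: with 44 evaluable patients, an unchanged cut-off of 38 would leave power of about 0.20. The article does not make clear how 55 allows for the loss.

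The arm-size figures rest on assumed block sizes and stratum shares, and on fully crossed factors. The power figures rest on the assumed 0.80. The type I error at 55 rests on neither.

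**What to change.** In Sample size {14}, replace the single cut-off by the smallest count with exact type I error at or below 0.05, given the 18/31 rule, for the SLPC number actually in the primary analysis:

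| SLPC patients analysed | Cut-off |
|---|---|
| 44–45 | 33 |
| 46 | 34 |
| 47–48 | 35 |
| 49 | 36 |
| 50–51 | 37 |
| 52 | 38 |
| 53–54 | 39 |
| 55 | 40 |
| 56–57 | 41 |
| 58–59 | 42 |
| 60 | 43 |

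Define that number as the evaluable or modified intention-to-treat patients, not simply those randomised: a cut-off of 40 applied with 44 evaluable patients has power of about 0.04 at 0.80. State whether 55 means enrolled or evaluable, and give the alternative rate used. Restate power for the size reached: about 0.89 to 0.96 at 0.80 for 50 to 60 patients, and 0.85 at 44. Fix the table before any SLPC outcome counts are seen.

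The cost is a short amendment and no extra patients. The threshold rises at 53 patients and above (from 38 to 40 at 55, where power falls from 0.980 to 0.931). If only 44 are evaluable, power falls short of the stated 0.90.

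Leave the stratification as it is. Enrolment began in April 2022, and dropping a factor mid-trial would change the randomisation while still not guaranteeing 55.

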### Concealment mechanisms {16b}

Randomization will be carried out using EnnovClinical software, *the e-CRF of CHU Nantes*, by connecting to the website at https://nantes-lrsy.ennov.com/EnnovClinical/login. The connection will be made using a login, a password, and a study number, issued by a data manager from the Sponsor Department. The enrolment number and randomization arm will be assigned automatically. Subjects are randomized into blocks as the allocation progresses. A block, *generated as already said by SAS*, being a subgroup of a predetermined size within which there is a random allocation of patients.

### Implementation {16c}

The randomization key is known only to the biostatistician and the data managers, to make it impossible for the investigator to assign a particular treatment. At the randomization visit, which can take place at the enrolment visit, the investigator will check the inclusion and *exclusion* criteria and then validate the randomization on the electronic Case Report Form (eCRF).

## Assignment of interventions: blinding

### Who will be blinded? {17a}

Our study is a randomized double-blind trial. Randomization will take place at the enrolment visit between D30 and D4. The patients and the investigators and their teams will be blind and will not know which treatment has been assigned.

### Procedure for unblinding if needed {17b}

Unnecessary or unintended decoding of the blinding should not occur during the study. If unblinding is deemed to be necessary for reasons of emergency, the investigator should send the completed “Unblinding Request Form” to the sponsor by email or by fax. The Coordination Committee will review the request. The coordinating pharmacy at CHU Nantes will have access to the correlation between the randomization number and the allocation for that person. If the request is approved, the results of any unblinding procedure will only be presented to the local Principal Investigator and the team treating the patient. In the case of a SUSAR, the vigilance team will unblind the treatment allocation for the regulatory process.

## Data collection and management

### Plans for assessment and collection of outcomes {18a}

Motor nerve conduction will be investigated for the median, tibial and fibular nerves, evaluating standard parameters: compound muscle action potential distal latency, baseline-to-negative peak amplitude and area, and motor nerve conduction velocity. Sensory nerve conduction will be recorded for the median, radial, and sural nerves, with sensory action potential peak-to-peak measurement. This EDX protocol will be performed three times for each patient, at the enrolment visit, at M4 (i.e., D1 of the ninth chemotherapy cycle), and at the end of the trial, 28 days after the last dose of SLPC/placebo.

Furthermore, we paired the ONLS questionnaire with the EDX. The ONLS scale is a disability questionnaire with a score that ranges from 0 (no disability) to 12 (severe disability). It has been validated in 100 patients with inflammatory polyneuropathy. It has a strong correlation (r = 0.97) with the Overall Disability Sum Score [14] and is widely used by neurologists assessing peripheral neuropathy.

Patients will complete another questionnaire during the trial, to measure their quality of life: QLQ-C30 version three [16]. Comprising 30 different items (questions), it is made up of 8 multi-item functional (physical, role, emotional, cognitive, and social) and symptom (fatigue, pain, and nausea) scales, one global health status and quality of life (QOL) scale, and 6 single items (dyspnea, insomnia, appetite loss, constipation, diarrhea, and financial difficulties). It covers the majority of the core symptoms recommended for patient-reported outcome measurement in cancer clinical trials [17].

### Plan to promote participant retention and complete follow-up {18b}

The target population of the trial is cancer patients during chemotherapy treatment; missing data could only result from withdrawal of consent or a serious adverse event (SAE). There is no plan for promoting participant retention.

### Data management {19}

An eCRF will be drawn up for each subject. Subjects will be identified using a code which should be the only information featuring in the eCRF, enabling a retrospective link with the patient.

The investigator will also encode the patient data in any documents that may be in their possession (EDX, questionnaires) and attached to the eCRF. At the end of the study, the CRF database and the safety database will be reconciled before the databases are locked. Similarly, an annual reconciliation will be carried out when updating the Annual Safety Report.

### Confidentiality {27}

Each patient's medical data will only be provided to the sponsor or any person duly authorized by the sponsor and, where applicable, to authorized health authorities, under conditions of confidentiality. The sponsor and the supervisory authorities may request direct access to medical records for the purposes of verification of the procedures and/or data in respect of the clinical trial, within the limits authorized by legislation and regulations. The data compiled during the trial may be processed electronically in compliance with CNIL requirements. CNIL is an independent administrative regulatory body whose mission is to ensure that data privacy legislation is applied to the collection, storage, and use of personal data.

### Plans for collection, laboratory evaluation, and storage of biological specimens for genetic or molecular analysis in this trial/future use {33}

Not applicable as no biological specimens were collected as part of this trial.

## Statistical methods

### Statistical methods for primary and secondary outcomes {20a}

Descriptive analyses will be conducted for all variables collected. Point estimates and 95% confidence intervals will be calculated for qualitative and quantitative variables. For estimates obtained using a small sample, the medians and interquartile intervals (for quantitative variables) and exact confidence interval (for qualitative variables) will be provided. All analyses will be performed with the use of R software (version 4.0) or SAS software (version 9.4).

To fulfill the main objective of this study, the prevalence of neurotoxicity of grade 2 or above in both arms will be estimated using linear mixed regression, taking into account the center effect (random effect). The second step will be to adjust this estimate based on known risk factors (gender, age, etc.).

For the secondary analyses:Comparison of time before cessation or reduction of chemotherapy treatment will be estimated using the Kaplan-Meier method and tested with the log-rank test;Comparison of patients with a decrease in treatment due to neurological toxicity will take place via mixed linear regression on both treatment arms;Progression of grades 3 and 4 neurological adverse events at baseline, M4, and M9 (or at the last visit if earlier) will be tested using mixed linear regression with a random center effect;EDX data will be compared using Fisher’s exact test and the Wilcoxon-Mann-Whitney test;The chi-square test or Fisher’s exact test will be used to compare Adverse Events in both arms;Progression of grades 3 and 4 neurological QLQ C30 at baseline, M4, and M9 (or at the last visit if earlier) will be tested via mixed linear regression with a random center effect; andMedian progression-free survival will be estimated and plotted using the Kaplan-Meier method and the response rate will be estimated as a percentage with a 95% confidence interval.

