### Trial design {8}

PROPERTY is a non-comparative, randomized (ratio 1:1), double-blind, multicenter placebo-controlled study. The trial was constructed like a phase 2 drug trial and is not powered for direct comparison between the two arms.

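### The log-rank test of time to cessation or reduction names no strata although randomisation is stratified; naming baseline neuropathy and age is a minor, cheap improvement

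*Protocol article*

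**What the plan says.** Sequence generation {16a} sets three stratification factors: "Randomization will be conducted blindly by center, neuropathy (stage 0 or 1), and age", with age cut at 65 years. Allocation is blocked: "It will be block balanced in a 1:1 ratio". Study setting {9} gives the number of centres: "Patients will be recruited from seven teaching hospital gastroenterology departments". The full cross-classification therefore has 7 × 2 × 2 = 28 cells.

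Statistical methods {20a} describes the time-to-event comparison in one clause: "Comparison of time before cessation or reduction of chemotherapy treatment will be estimated using the Kaplan-Meier method and tested with the log-rank test". Strata and covariates are not mentioned there. The same section does name adjustment elsewhere: a random centre effect for the primary analysis, for grade 3-4 neurological events and for quality of life, and known risk factors, including gender and age, as a second step for the primary estimate.

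Trial design {8} calls the trial non-comparative and says that it "is not powered for direct comparison between the two arms". Sample size {14} fixes the size: "55 patients will be enrolled in each arm, that is to say, 110 patients".

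**The concern.** When allocation is balanced within strata and the strata predict the outcome, the variance used by an ordinary log-rank test includes between-stratum variation that the design has already removed from the treatment contrast. The test then rejects less often than its nominal level under the null. Pooling patients with different hazards also dilutes the treatment effect over time. A stratified log-rank test compares patients within strata and avoids both effects.

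There is a reason to think that baseline neuropathy matters here. Table 1 admits patients with neuropathy up to grade 1, and in Table 4 the oxaliplatin adjustment depends on the neurotoxicity grade, with no reduction at grade 1 and reductions starting at persistent grade 2. A patient entering at stage 1 is thus one grade from a trigger. The protocol also counts age among the known risk factors.

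This is the only time-to-event outcome for which a between-arm test is specified; progression-free survival is only estimated. With 110 patients the number of events will be modest, so any information already held in the randomisation record is worth using.

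**Working it through.** **No figure of the plan to reproduce.** The article states no event count, hazard ratio or power for this comparison. Its only design calculation is for the primary endpoint and does not bear on this point.

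**Scale.** Schoenfeld's formula for two equal arms gives d = 4(1.960 + 0.842)² / (ln HR)². For HR 0.5 and 80% power, d = 4 × 7.85 / 0.480 ≈ 66 events. The same formula gives power 0.592 with 40 events and 0.729 with 55.

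**Tests compared.** With arm indicator g, event indicator d, and e the share of those at risk who are on SLPC, U = Σ d(g − e), V = Σ d·e(1 − e) and Z = U/√V. The stratified test computes U and V within each stratum and adds them before dividing. Both reject when |Z| > 1.96.

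**Inputs from the article.** N = 110, 1:1 allocation in blocks, 7 centres, neuropathy 0/1, age below or from 65.

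**Assumed inputs (not in the article).** Block size 4 within the 28 cells; 20% at stage 1; 50% aged 65 or over; median time to event 5 months in the reference group; 6 months of observation; 20% dropout by month 4; treatment HR 0.5 for power and 1 for size; prognostic hazard ratios varied.

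**Results.** The first four rows use 9,000 simulated trials each. The last uses 4,000 and adds a centre effect with SD 0.4 on the log-hazard scale.

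| Prognostic HR (neuropathy / age) | Size, unstratified | Size, 4 strata | Power, unstratified | Power, 4 strata | Change (points) | Power, 28 strata |
|---|---|---|---|---|---|---|
| 1 / 1 | 0.050 | 0.049 | 62.4% | 61.3% | −1.1 | 53.0% |
| 1.5 / 1.2 | 0.048 | 0.050 | 65.7% | 64.8% | −0.9 | 55.4% |
| 2 / 1.3 | 0.047 | 0.048 | 66.3% | 67.3% | +1.0 | 56.8% |
| 3 / 1.5 | 0.042 | 0.047 | 65.9% | 70.6% | +4.7 | 59.9% |
| 3 / 2, plus centre | 0.033 | 0.044 | 63.6% | 70.0% | +6.4 | 62.9% |

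The first four power scenarios had on average 43 to 57 events. The Monte Carlo standard error of a size near 0.05 with 9,000 trials is √(0.05 × 0.95 / 9,000) = 0.0023, so 0.042 lies about 3.5 standard errors below nominal.

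**Varying the stage 1 share from 10% to 40%.** Stratified minus unstratified power was −1.4 to −0.9 points with uninformative strata, −0.8 to +1.6 at 2 / 1.3, and +1.4 to +8.3 at 3 / 1.5. The unstratified size fell to 0.036 when the strata were strong and the stage 1 share large.

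**A second event model** (hazard 0.06 per cycle, 12 cycles, 2% dropout per cycle, age HR 1.0 or 1.3). With only 5-10% at stage 1, the change was −1.6 to +0.1 points at neuropathy HR 1-2 and 0 to +0.9 at HR 3. At a 40% share and HR 3 it was +6.6 to +7.5.

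**Why centre is left out.** 110 / 28 = 3.9 patients per cell, so many events occur in cells with only one arm still at risk and add nothing to U or V. In the four rows without a centre effect, stratifying by all 28 cells loses 6 to 10 points against the unstratified test. Four strata average 110 / 4 = 27.5 patients.

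**The case against.** The strongest reply is that nothing here is an error. The article does not say that the test will be unstratified. A condensed article often leaves the strata of a secondary test to the analysis plan, which is not available here. An unstratified log-rank test after stratified randomisation is valid, any departure is in the conservative direction, and the trial is declared not powered for comparing the arms.

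Most of that stands. A reader might infer that the plan has decided to ignore the strata. The wording does not establish this, although naming adjustment for several neighbouring analyses and none for this one makes an unstratified test the natural reading.

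A reader might also infer that the test is conservative in any case and that stratifying recovers power for free. Neither follows. Both depend on prognostic strength, which the article does not give, and stratifying on uninformative factors loses about 1 point.

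The event itself also weakens the argument. Outcomes {12} and Statistical methods {20a} do not restrict it to neurological causes, and decreases due to neurological toxicity are analysed separately. Events from haematological, gastrointestinal or other causes would dilute the effect of baseline neuropathy, so a hazard ratio of 3 may be optimistic. The stage 1 share could also be small, since patients are untreated for metastatic disease and prior oxaliplatin is excluded.

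Finally, dropping centre means that the analysis does not mirror the randomisation in full. That is a judgement, supported by the sparse cells.

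What remains is an uneven trade: about 1 to 2 points at worst against up to about 8 if the strata are strong, using data already held.

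**Conclusion.** The point holds as a minor improvement. The log-rank test as written is valid and carries no added false-positive risk. Under assumed prognostic hazard ratios of 3 for neuropathy and 1.5 for age, with 10-40% of patients at stage 1, stratifying by these two factors gains about 1 to 8 points of power. With weak to moderate effects (up to about 2 and 1.3) the difference is within about 1 to 2 points either way, and with uninformative strata the cost is about 1 point. All these figures also assume the event rate, the dropout and a treatment hazard ratio of 0.5.

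The documents do not support describing this as a loss of planned power or a threat to the trial's conclusions. The outcome is secondary, no power was set for it, and the primary conclusion is unaffected.

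**What to change.** In Statistical methods {20a}, state that time to cessation or reduction is tested with a log-rank test stratified by baseline neuropathy (0/1) and age (<65/≥65), and that the hazard ratio with 95% confidence interval comes from a Cox model stratified the same way. Use these four strata only, say that centre is omitted because the 28 cells are too sparse, and keep the unstratified Kaplan-Meier curves for display. If an unstratified test is intended, say so explicitly.

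The cost is one sentence, fixed before unblinding. Both factors are already in the randomisation record, so no new data are needed.
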